## Abstract

**Background:**

Changes in response patterns of biological stress systems, including responses of the sympathetic nervous system (SNS) and the hypothalamus–pituitary–adrenal (HPA) axis to repeated stress, can promote the development and progression of chronic diseases via changes in downstream inflammatory processes. The aim of this project is thus to investigate, whether habituation of biological stress system activity including responses of the inflammatory system can be modified. Aiming to test for possible paths of action, a randomized controlled study with two intervention programs designed to manipulate cognitive coping strategies will be carried out. By increasing either ruminative or self-compassionate thoughts among healthy young adults, the intervention programs are expected to affect the regulation of occurring emotions as expressed by the responsiveness of biological systems during repeated stress exposure.

**Methods:**

In this study, a total of 120 healthy adults will complete the Trier Social Stress Test (TSST) on two consecutive days. Immediately after the first stress induction, participants will be randomly assigned to two experimental conditions designed to manipulate cognitive coping strategies (rumination vs. self-compassion) or a control condition. Measures of HPA axis (salivary cortisol) and autonomic activity (salivary alpha amylase, heart rate, heart rate variability) as well as inflammatory markers (plasma interleukin(IL)-6, expression rates of pro- and anti-inflammatory cytokine genes) will be repeatedly assessed throughout the experimental sessions. Response and habituation indices of these measures will be calculated and compared between the experimental conditions and the control condition.

**Discussion:**

The results should provide insight into whether modifying response patterns of biological stress systems could reverse a significant biological mechanism in the development of stress-related diseases.

**Trial registration:**

German Clinical Trials Register (DKRS), DRKS00034790. Registered on August 12, 2024, https://www.drks.de/DRKS00034790.

**Supplementary Information:**

The online version contains supplementary material available at 10.1186/s13063-024-08620-w.

## Introduction

### Background

Psychological stress experience has become a serious issue in modern society and is a major cause of physical health impairments. The impact of psychological stress is also gaining significant importance in the workplace: as exemplified by German health insurance companies, the number of days absent due to mental disorders increased by 48.4% between 2012 and 2022 [1], resulting in costs amounting to billions for companies and the economy. In recent years, German healthcare costs of mental illnesses amounted to 56.4 billion euros in 2020 [2] and 15.8 billion euros in lost production costs were recorded in 2021 [3]. However, since mental disorders, such as frequent and chronic stress experience, also contribute to the development of numerous somatic diseases [e.g., cardiovascular diseases, 4], it is expected that the negative economic consequences may even aggravate due to long-term effects of psychological stress on physical health. Counteracting these effects in the long-term by designing effective health-promoting intervention programs requires an understanding of underlying biological processes. Thus, the proposed project aims to investigate whether biological adaptation to repeated stress and associated pathophysiological processes can be modified.

Altered activity of biological stress systems, including the hypothalamus–pituitary–adrenal (HPA) axis, the sympathetic nervous system (SNS), and the inflammatory system, is considered to play a mediating role between stress experience and pathophysiological processes [5]. While an effective interplay of these systems and the resulting endocrine and inflammatory responses contribute to enhanced immune functions during acute stress exposure [6], dysregulations of these systems, caused for example by repeated or long-term stress experience, may lead to adverse health effects [7]. For instance, a derailment of the inflammatory system—a consequence of chronic stress experience—has been established as a significant contributor to the development of important non-communicable diseases such as cardiovascular diseases, metabolic diseases as well as some cancers [8, 9].

Within the framework of the allostatic load model [10, 11], which posits a causal relationship between maladaptive stress response patterns and the development of diseases, McEwen [7] describes the lack of habituation of biological stress responses to repeated stressors as a potential mechanism that plays a crucial role in disease progression. More specifically, non-habituation is considered a dysfunctional adaptation mechanism to repeated stressful events leading to wear and tear on the system over time and consequently to an accumulation of allostatic load. Conversely, biological responses being able to habituate to recurrent stressors (i.e., to adapt) are seen as a protective factor against the accumulation of allostatic load. Accordingly, the extent to which an individual’s biological stress response habituates to repeated stress is regarded as a determinant for long-term health [12].

A large number of studies has revealed associations between stronger habituation of biological stress system activity and various biopsychosocial determinants, including, for example, self-compassion [13], rumination [14], emotion regulation [15], gender [16], and resilience [17], whereas experimental research designed to increase habituation ability is scarce. For instance, Manigault et al. [18] attempted to modify HPA axis activity in response to repeated stress and reported increased HPA axis habituation in a population of healthy adults after being exposed to either a 6-week mindfulness-based stress reduction intervention (*n* = 31) or a 6-week cognitive-behavioral stress management intervention (*n* = 34). Similarly, Asbrand et al. [19] attempted to increase HPA axis habituation to repeated stress in socially phobic children (*n* = 32), demonstrating that, upon completion of 12 weeks of cognitive–behavioral stress management intervention, cortisol responses remained either robust (i.e., did not change in their intensity) or decreased over repeated stress exposure. As demonstrated by these experiments, psychotherapeutic intervention measures therefore prove to be an effective method for modification of biological stress system activity. Accordingly, cognitive–behavioral techniques (e.g., cognitive restructuring, relaxation, and self-regulation strategies) may facilitate cognitive reappraisal of anxiety-inducing stimuli and down-regulation of upcoming specific emotions during psychosocial stress, resulting in altered stress response patterns of HPA axis activity as expressed by higher HPA axis habituation to repeated stress [18].

### Summary and objective

In summary, habituation of biological stress system activity to repeated stress exposure is considered a protective mechanism counteracting the accumulation of allostatic load [12]. While determinants of biological stress response habituation have been studied in depth [e.g., 17], only few experimental studies have addressed the modifiability of biological stress response patterns by promoting biological stress response habituation [18, 19]. As shown by these studies, habituation of HPA axis activity to repeated stress can be successfully increased in both healthy individuals and socially phobic children using psychotherapeutic techniques [18, 19]. However, due to the scarcity of studies demonstrating that psychotherapeutic intervention programs may effectively modify habituation of biological stress system activity, it remains unclear whether stress response habituation of other health-relevant systems, including the SNS and in particular the inflammatory system, may be targeted using equivalent interventional approaches.

Following this line of reasoning, we developed a randomized controlled procedure which addresses the manipulation of coping strategies, which in turn are expected to affect the regulation of occurring emotions as expressed by the responsiveness of biological stress systems during repeated stress exposure. To investigate possible paths of action, the intervention program aims to manipulate two different coping strategies that have been shown to be either positively [self-compassion, 13] or negatively [rumination, 14] related to biological stress response habituation. Subsequently, we aim to test whether the manipulation of coping strategies causes changes in the habituation capacity of biological stress system activity. For this purpose, stress-induced changes of endocrine, autonomic, and inflammatory parameters will be assessed in order to determine the effects of psychological coping on biological stress response habituation and, in particular, the ability to modify stress-induced inflammatory response patterns. Overall, we anticipate self-compassion to promote and rumination to impede biological stress response habituation. Our specific hypotheses are specified in the “Methods” section below (see “Hypotheses”).

## Methods

### Study design

The study is designed as a randomized controlled, single-center, and single-blinded trial, in which participants will be randomly assigned to one of two intervention groups (rumination vs. self-compassion) or a control condition (see “Randomization”) with an allocation ratio of 1:1:1. The study employs a superiority trial design, aiming to determine whether one of the two cognitive coping interventions is more effective in modifying the responsiveness and habituation of biological stress systems compared to the control condition. The design encompasses repeated measurements of each group, i.e., each group will undergo two experimental sessions (t1 and t2) comprising stress test exposures, and within each experimental session, repeated biological and psychological outcome assessments will take place (see Table 1).

**Table 1 Tab1:**
[figure not shown]
Study time line for the schedule of enrolment, experimental conditions, and assessments

*ADS-L* Allgemeine Depressionsskala Langform, *BMI* Body Mass Index, *BSRI* Brief State Rumination Inventory, *HPA axis* hypothalamus-pituitary adrenal axis, *HR* heart rate, *HRV* heart rate variability, *IкB* I kappa B kinase, *IL* Interleukin, *NF-кB* nuclear Factor kappa B, *PANAS* Positive and Negative Affect Schedule, *PASA* Primary Appraisal Secondary Appraisal, *PSS* Perceived Stress Scale, *SCS-D* Self Compassion Scale Deutsch, *RSQ* Response Style Questionnaire, *sAA* salivary alpha-amylase, *SPS* Social Phobia Scale, *SIAS* Social Interaction Anxiety Scale, *SSCS-S* State Self-Compassion Scale Short Form, *SSSQ-G* Short Stress State Questionnaire German

### Participants

A total of *N* = 120 (*n* = 40 per condition) community-dwelling adults from the Nürnberg/Fürth/Erlangen region (Bavaria, Germany) will be recruited via advertisements and offered monetary compensation (50 Euros) if included in the study. Before testing, participants receive information sheets via email and will have the possibility to contact study staff with any queries. Participants will then be screened for eligibility using EFS Survey Unipark (Tivian XI GmbH, Cologne, Germany), which will continue until the target population is achieved. Written informed consent will be obtained electronically from each participant at the beginning of the screening process.

Eligible participants must be at least 18 years old and willing to participate in the study and provide biological samples. Female participants will be tested in the luteal phase of their menstrual cycle. Exclusion criteria are (1) younger than 18 years of age, (2) presence of depressive or social anxiety symptomatology, (3) presence of acute and/or chronic somatic diseases, (4) medication intake (e.g., beta blocker, glucocorticoids, anti-depressants), with the exception of hormonal contraceptives in women, (5) body mass index (BMI) below 18 or above 30 kg/m^2^, (6) smoking (> 10 cigarettes/week), (7) receiving psychotherapeutic treatment at study entry, (8) previous experience with the stress protocol, and (9) being an employee of Friedrich-Alexander-Universität Erlangen-Nürnberg (FAU). For an overview of the enrolment procedure, see Fig. 1.

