### Hypotheses

By increasing either ruminative or self-compassionate thoughts among healthy young adults, the intervention programs are expected to affect the regulation of occurring emotions as expressed by the responsiveness of biological systems during repeated stress exposure.

To check whether the experimental manipulations are successful on a psychological level, self-report measures will be assessed repeatedly over the course of each experimental session and are expected to change over the course of experimental sessions 1 and 2. Specifically, we hypothesize that stress will elicit changes in affect scores and stress appraisals, whereas the two intervention programs are expected to induce changes in affect, self-compassion and rumination, which will be stronger than in the control group (no intervention). Furthermore, we expect these variables to predict indicators of biological stress system activity.

Hypothesis 1: Independent of experimental session and group, stress will elicit significant increases of negative affect and stress appraisals as well as decreases of positive affect.Hypothesis 2: At experimental session 1, stress-induced changes of positive and negative affect and stress appraisals will be indifferent between participants from intervention groups 1 (rumination) and 2 (self-compassion) as well as participants from the control group (no intervention).Hypothesis 3: At experimental session 2, stress-induced decreases of positive affect as well as increases of negative affect and stress appraisals will be strongest in participants from intervention group 1 (rumination) and lowest in participants from intervention group 2 (self-compassion).Hypothesis 4: Increases in state self-compassion and positive affect from pre- to post-intervention will be strongest in intervention group 2 (self-compassion), and increases in state rumination and negative affect will be strongest in intervention group 1 (rumination).

Furthermore, we expect significant responses of biological stress system activity in all experimental groups at each experimental session. Specifically, we expect responses of biological stress system activity to be similar at experimental session 1 and participants from intervention group 2 (self-compassion) to show stronger habituation of stress system activity compared to intervention group 1 (rumination) or the control group (no intervention).

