### Data preparation and statistical analysis

Data preparation and statistical analysis will be performed using IBM SPSS Statistics 26 (IBM Corp., Armonk, NY, USA). Following our pre-registered analysis plan [60], data will be screened for outliers using *z*-scores, and outliers which differ more than 3 standard deviations from the participants’ mean will be excluded from further analysis. In addition, participants will be excluded in case of elevated cortisol levels (e.g., > 12 nmol/L or *z* > 3.29) after arrival at the laboratory (i.e., at baseline) and after accommodating to the testing situation (i.e., at − 1 min relative to the TSST). Additionally, non-adherent participants whose missing values exceed 25% of the data will also be excluded from the analysis. In the next step, Kolmogorov–Smirnov tests will be conducted in order to check for normal distribution. If necessary, data will be log-, ln-, or inverse transformed to reduce skewness of biological data.

To analyze the data (i.e., to compare self-report measures as well as biological response and habituation indices between experimental groups), we will use separate analyses of covariance (ANCOVAs). Sex and BMI will be used as covariates in analyses of biological data, as these two variables have been repeatedly shown to be highly relevant for stress system activity [61, 62]. We will use the standard *p* < 0.05 criteria for determining if the ANCOVA and the post hoc test suggest that the results are significantly different from those expected if the null hypothesis were correct. The post-hoc Bonferroni test adjusts for multiple comparisons.

To investigate associations between primary psychological outcome measures and indices of biological stress measures, we will compute separate hierarchical linear regression models, regressing biological outcome measures onto psychological outcome variables. Again, sex and BMI will be included as covariates in these analyses. When examining state variables, the respective trait variable will be included as covariate in regression analyses.

We expect that certain psychological (e.g., emotion regulation, coping), demographic (e.g., age, gender, sex), and anthropometric (e.g., BMI) variables may be related to biological stress system activity. Therefore, we will test for relationships between these variables and primary outcome measures of biological stress responses in an exploratory fashion.

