### Limitations

One major limitation of the present study is that we will not be able to control for the effects of leukocyte trafficking, which implies that the changes observed cannot be clearly attributed to either stress-induced migration of leukocytes with activated inflammatory mechanisms into peripheral blood or the actual activation of the inflammatory cascade within the individual leukocytes [63, 64]. Future studies will need to control for effects of leukocyte trafficking using appropriate laboratory techniques ahead of RNA extraction.

Furthermore, eligible participants for the study will likely be younger than 40 years of age and generalizability of the results will be limited to some extent. However, our target sample represents a young and healthy population from which we would expect minor risk of morbidity being associated with dysregulations of biological stress systems including, for example, major depression [37], chronic fatigue [65], hypertension [66], or the metabolic syndrome [67]. Future studies should investigate whether the findings derived from this study generalize to more diverse populations, including individuals from other groups of age (e.g., above 40 years), or to individuals with existing health conditions related to stress system dysregulation. Furthermore, longitudinal studies are needed to further investigate how rumination and self-compassion might affect immune-mediated effects on physiological functions and physical health in later life.

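### The entry criteria admit any adult from 18 upwards, not only the young adults described, and age is left out of the covariate set although the protocol expects it may matter

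*Protocol article*

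**What the plan says.** **Who can enter (Participants).** The only age rule for inclusion is a minimum: "Eligible participants must be at least 18 years old and willing to participate in the study and provide biological samples". The exclusion list mirrors it ("Exclusion criteria are (1) younger than 18 years of age"), and none of its nine items caps age. Recruitment is by advertisement to community-dwelling adults.

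**Who is described.** The lead-in to the Hypotheses section, like the Abstract, places the expected effects in young adults: "By increasing either ruminative or self-compassionate thoughts among healthy young adults". The Limitations section says that "eligible participants for the study will likely be younger than 40 years of age" and that "our target sample represents a young and healthy population". It leaves people above 40 to future studies.

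**How age is handled (Data preparation and statistical analysis; Randomization).** For the group comparisons, "Sex and BMI will be used as covariates in analyses of biological data". The hierarchical regressions use the same two covariates, plus the matching trait measure when a state measure is examined. The analysis section expects that demographic variables, with age named first, may be related to stress-system activity, but assigns them to exploratory analysis. Randomization is stratified by sex only.

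**The concern.** Two things do not fit together. First, the population is described as young, but that rests on a forecast about who will volunteer and not on a criterion. If older volunteers come forward, they are eligible and the sample is no longer the one described. Second, the protocol names age as a possible correlate of its biological outcomes and then leaves it out of every confirmatory model for them, while the open criterion sets no limit on how widely age can vary.

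This is not a matter left to an unseen analysis plan, because the article states the covariate set. Two consequences are possible. Age-related variance would stay in the error term of the ANCOVAs. And the regressions for Hypotheses 9 and 10 relate self-reported rumination, self-compassion, affect and appraisal to biological responses and habituation. Individual differences in those predictors are not randomized, so age could be associated with both sides of the relation.

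**Working it through.** **1. Criterion against description.** Participants: 18 or over, no upper bound. Abstract and Hypotheses: young adults, with no number. Limitations: probably under 40, worded as an expectation. The figure 40 appears only in the Limitations. A healthy, unmedicated 60-year-old man meets every listed criterion and lies outside the population described. The exclusions for disease and medication make such entrants fewer but do not bar them.

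**2. The plan's own sample size.** Inputs from the Power analysis section: three groups, alpha 0.05, power 0.80, effect size 0.30. For a one-way ANOVA F test the noncentrality is N × f². With f = 0.30 and N = 111 this is 111 × 0.09 = 9.99 on 2 and 108 degrees of freedom, and power is 0.8035. So N = 111 is reproduced. (The article labels the effect f²; read literally, f² = 0.30 would need only N = 36, so f = 0.30 was evidently used. Nothing here depends on that label.)

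**3. Cost of adding age.** Each covariate removes one error degree of freedom. With N = 111 and f = 0.30:

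| Covariates | Error df | Power |
|---|---|---|
| 0 | 108 | 0.8035 |
| 1 | 107 | 0.8034 |
| 2 (sex, BMI) | 106 | 0.8033 |
| 3 (sex, BMI, age) | 105 | 0.8032 |

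**4. What leaving age out could cost the arm comparisons.** The documents give no figure for the association of age with any outcome, so this is an assumption shown over a range. Suppose age accounts for a share s of the error variance, over and above what the planning value allowed for. The effective effect size is then 0.30 × √(1 − s). For s = 0.05 that is 0.30 × √0.95 = 0.2924.

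| s | Effective f | Power at N = 111 | N for 80% power, equal groups |
|---|---|---|---|
| 0.02 | 0.297 | 0.795 | 114 |
| 0.05 | 0.292 | 0.782 | 117 |
| 0.10 | 0.285 | 0.758 | 123 |
| 0.15 | 0.277 | 0.732 | 129 |

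A correlation of 0.2 to 0.3 between age and an index would correspond to s = 0.2² = 0.04 to 0.3² = 0.09. The lower rows are probably pessimistic. The response indices are peak minus pre-stress values, and the habituation indices are differences between two responses of the same person, so stable age differences in level largely cancel.

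**5. Hypotheses 9 and 10.** In standardized terms, after sex and BMI are partialled out, omitting age shifts a predictor's coefficient by (age's own coefficient) × (correlation of age with the predictor). If both were 0.2 to 0.3 in absolute value, the shift would be 0.2 × 0.2 = 0.04 to 0.3 × 0.3 = 0.09, in either direction. These values too are assumptions, and both factors shrink if the enrolled age range is narrow. Unlike the loss in step 4, this is a bias, and randomization does not remove it.

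**The case against.** The strongest reply is that this is a mismatch of wording, partly disclosed, with little effect on the trial's main comparisons. Much of that stands.

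- **Randomization.** Age cannot bias the arm contrasts systematically, and chance imbalance is already covered by the test's error rate. This stands, but it does not reach the associations in Hypotheses 9 and 10.
- **The hypotheses do not say under 40.** A reader might infer that under 40 is the protocol's target and that the criteria break it. The documents do not support this. The hypotheses give no age, and the figure 40 appears only as a forecast in the Limitations section, which also concedes limited generalizability.
- **Older women.** A reader might also infer that the older age range is open only to men, because "Female participants will be tested in the luteal phase of their menstrual cycle". The documents do not support this either. The sentence concerns when women are tested and is not one of the exclusion criteria. Menopause is not mentioned, and users of hormonal contraceptives are admitted, so how the rule applies to women without a natural cycle is not settled in this article.
- **Covariate choice.** Sex and BMI were chosen with a stated reason, and age was deliberately made exploratory. That is defensible. But the protocol itself expects age may be relevant, and adjustment is practically free.
- **Changing a pre-registered plan.** The analyst knows the allocation, and strict adherence to the registered plan is the stated safeguard. This stands and governs the timing: a covariate added after the data have been seen would weaken that safeguard, whereas a dated amendment beforehand does not.

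**Conclusion.** The point holds in limited form. The criteria do not deliver the young population described in the Abstract and Hypotheses, and age is missing from the biological models although the protocol itself regards it as a possible correlate. The arm comparisons remain valid. Their loss is one of precision, of unknown size and possibly small: about 0.01 in power at 2% of error variance and about 0.05 at 10%, both assumed. The firmer reason to adjust is the possible confounding by age in Hypotheses 9 and 10, also of unknown size. The conclusion rests on the text and on the near-zero cost of adjustment, not on any assumed correlation. This is an inexpensive improvement and a wording correction, not a flaw that threatens the trial.

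**What to change.** 1. **Covariates.** By a dated amendment to the pre-registered plan, made before any data are analysed, add age to sex and BMI in the ANCOVAs of biological outcomes and in the hierarchical regressions. Age is already collected at screening. The cost is one degree of freedom per model (power 0.8033 to 0.8032 at N = 111). The protocol schedules data collection to September 2026 with no preliminary analyses, and its Ethics approval section already provides for notifying amendments.
2. **Population wording.** Reconcile the description with the criterion of 18 or over, for example by dropping the word young from the Abstract and the Hypotheses section and reporting the achieved age range by arm and sex. The cost is editorial.
3. **Upper age limit.** This is optional. It would make the sample match the description for the remaining enrolment, at the price of narrower generalizability. It is for the sponsor to decide and is not a required correction.

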### Assessment of sample characteristics during screening

Demographic (e.g., age, gender, sex), socioeconomic (e.g., occupation), anthropometric (e.g., BMI), health-related (diseases, medication intake), and biobehavioral (e.g., smoking status) variables will be electronically assessed during screening and will partly be used to determine eligibility for participation (see “Participants”).

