### Randomization

Before testing, eligible patients will be randomized and stratified for sex using the Robust Randomization App (RRApp, Version 3.0.1). A principal investigator, who is independent of the enrollment and data collection, will be responsible for the randomization process. He will store the randomization lists in sealed envelopes and hand them out to staff members immediately before the experimental sessions begin. Participants will be blinded and will not know the experimental condition to which they have been assigned. Staff members will be encouraged to maintain blinding as far as possible. The actual allocation will not be disclosed to the participants, and any code breaks must be promptly reported, along with the reason for the breach. Unblinding of participants will result in study discontinuation. To assess the effectiveness of the blinding procedures, as well as to gain insight into participant perceptions of their assigned interventions, participants will be asked whether they have any suspicions about which intervention group they have been assigned to upon completion of all laboratory sessions. As the analyst is also involved in the data collection process and therefore possesses knowledge of the participants’ group assignments, no double-blinding will be implemented for the data analysis. This potential for bias will be mitigated by adhering strictly to the pre-registered analysis plan [60], which outlines the statistical methods and criteria for evaluating outcomes.

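### The luteal-phase rule cannot standardise users of ovulation-suppressing contraceptives, whom the protocol admits, and the analysis separates participants by sex only: a modest, avoidable loss of precision, not a bias

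*Protocol article*

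**What the plan says.** All references are to the protocol article.

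- **Participants, timing rule:** "Female participants will be tested in the luteal phase of their menstrual cycle". No exception is stated.
- **Participants, exclusion criterion 4:** medication intake excludes a person, "with the exception of hormonal contraceptives in women". Users are therefore eligible, and no separate timing is given for them.
- **Randomization:** "eligible patients will be randomized and stratified for sex using the Robust Randomization App". No other stratification factor is named.
- **Data preparation and statistical analysis, group comparisons:** "Sex and BMI will be used as covariates in analyses of biological data".
- **Same section, regressions:** "Again, sex and BMI will be included as covariates in these analyses". The matching trait score is added when a state variable is examined.
- **Same section, exploratory analyses:** the examples cover psychological variables and "demographic (e.g., age, gender, sex), and anthropometric (e.g., BMI) variables may be related to biological stress system activity". Contraceptive use is not among them.
- **Assessment of sample characteristics during screening:** "health-related (diseases, medication intake), and biobehavioral (e.g., smoking status) variables will be electronically assessed during screening". Contraceptive use can therefore be known before randomization.

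**The concern.** A luteal-phase rule has a purpose only if female hormonal state is thought to influence the stress outcomes. The protocol accepts that premise and then admits a group of women for whom the rule cannot do its work. An ovulation-suppressing contraceptive removes the natural luteal phase, so a visit date chosen by cycle day does not put such a woman in the same state as a naturally cycling woman. Nothing later in the design recovers the distinction, because both groups are simply female in the stratification and in the models.

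Two things are at stake. If users and non-users differ in their biological responses, that difference stays in the error term although a covariate could remove it. If the arms differ by chance in their number of users, the contrast between arms is not corrected for it.

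**Working it through.** **1. The two eligibility statements side by side.** The timing rule covers all women. The medication exception brings in women of whom some have no natural luteal phase. For those women the rule cannot be met as written. That ovulation-suppressing methods leave no natural luteal phase is general physiology, not a statement in the protocol, and it need not hold for every hormonal method.

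**2. The plan's own sample size.** Power analysis gives N = 111 for three groups, α = 0.05 and power 0.80. The check uses the omnibus F test with noncentrality λ = N·f². With f = 0.30, λ = 111 × 0.09 = 9.99 and power is 0.803, so N = 111 is reproduced. (The text prints 0.30 as f²; read that way, N would be 36. The present point does not depend on this.)

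**3. Cost of one more covariate degree of freedom at N = 111, f = 0.30.** Power is 0.8033 with two and 0.8032 with three. The required N stays at 111.

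**4. Variance left in the error term.** The documents give neither the share of women, nor contraceptive use, nor its effect. Assumed ranges:

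- share of women w = 0.50-0.65
- share of women using hormonal contraception p = 0.30-0.50
- user versus non-user difference e = 0.3-0.8 SD

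Variance beyond sex = w·p·(1−p)·e².

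- Low end: 0.50 × 0.30 × 0.70 × 0.09 = 0.009
- High end: 0.65 × 0.50 × 0.50 × 0.64 = 0.104

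That is about 1-10% of outcome variance.

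**5. Effect on power.** If f = 0.30 holds with contraceptive status removed, omitting it gives f′ = 0.30/√(1 + variance from step 4).

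| Case | f′ | Power at N = 111 |
|---|---|---|
| Status adjusted for | 0.300 | 0.803 |
| Low end, 0.009 | 0.299 | 0.799 |
| High end, 0.104 | 0.286 | 0.761 |

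The high end needs all three assumptions at their extremes. These figures apply to an index in which users and non-users actually differ by e.

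**6. Chance imbalance.** With 20-26 women per arm of 40 and p = 0.30-0.50, user counts were simulated as binomial in three arms.

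| Event | Probability |
|---|---|
| Highest and lowest arm differ by 5 or more users | 26-42% |
| Highest and lowest arm differ by 6 or more users | 14-28% |
| One given pair of arms differs by 6 or more users | 6-13% |

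The shift in a contrast is (gap/40)·e. For a gap of 6 it is 0.15 × 0.3 = 0.045 SD to 0.15 × 0.8 = 0.12 SD. The average absolute shift for a given pair of arms is about 0.02-0.06 SD. The preliminary effects quoted in Power analysis are d = 0.67 and d = 0.81.

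**7. Which hypotheses are exposed.** Outcome measures defines the habituation index as the first stress response minus the second in the same person. A user/non-user offset that is equal on both days cancels in that difference. Hypothesis 7, on session 2 responses, is exposed to such an offset. Hypothesis 8, on habituation, is exposed only if habituation itself differs by contraceptive status.

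**The case against.** The strongest reply has four parts.

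- **Condensed text.** An article need not spell out how contraceptive users are scheduled, and a reader may take the luteal rule to mean only women who have a luteal phase. This has force, and it limits the scheduling part to reconciling two sentences. It does not support the inference that sites cannot schedule users, or that they will use a meaningless calendar; the protocol says neither. It also does not help the analysis, where the covariates are named and do not separate the two groups.
- **No bias.** Randomization balances contraceptive use in expectation, and leaving out a prognostic covariate neither biases the comparison nor inflates type I error. This stands in full. A reader might infer that the arm comparisons are systematically distorted; nothing in the protocol supports that.
- **Small and assumed size.** The ranges come from outside the documents, a six-user gap in a given pair of arms is uncommon, and the usual shift is small beside the planning effects. This stands too. A reader might also carry the same figures over to Hypothesis 8, but the within-person difference removes a stable offset, and the power analysis was itself based on habituation.
- **Pre-registration.** The pre-registered plan is not shown and may deal with contraceptive use. Changing a named covariate also has a cost in credibility, since Randomization states that the analyst knows the group assignments and relies on strict adherence to that plan. The first part is possible, although the article says it follows that plan and names only sex and BMI. The second part bears on how and when the change is made, and is a reason to make it formally before any analysis.

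**Conclusion.** The point holds in a limited form. The hormonal standardisation that the protocol chose does not reach users of ovulation-suppressing contraceptives, whom it admits, and neither the stratification nor the models make up for this. The consequence is lost precision and uncorrected chance imbalance, chiefly for the response indices. Under the assumed ranges it amounts to 1-10% of outcome variance, at most about four percentage points of power, and an average shift of 0.02-0.06 SD in a given contrast. With smaller true differences it would be negligible. It is worth correcting because the remedy costs almost nothing and medication intake is already recorded, not because the trial's conclusions are endangered.

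**What to change.** 1. **Participants.** Reconcile the luteal-phase sentence with the contraceptive exception, so that it is clear which women the rule covers and that users have a stated timing rule. Its content is for the investigators to decide.
2. **Data preparation and statistical analysis, and the pre-registered plan.** By a dated amendment before any data are analysed, replace the covariate sex in the biological models with a three-level factor: men; naturally cycling women; hormonal-contraceptive users. Derive it from the medication data recorded at screening. The protocol places analysis after the end of data collection with no preliminary analyses, so there is still room to do this cleanly.
3. **Sensitivity analysis.** Report the sex-and-BMI model alongside, so that readers can see whether the change matters.

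Stratification by sex can stay. The cost is one degree of freedom (power 0.8033 to 0.8032 at N = 111) and a documented change to the pre-registered plan, with no added participants or procedures. The three-level factor still pools different kinds of hormonal contraceptive, so it reduces the mixing without removing it.
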